## Abstract

**Introduction:**

In conjunction with a beta-lactam, aminoglycosides are the first-choice antibiotic for empirical treatment of sepsis in the neonatal period. The m.1555A>G variant predisposes to ototoxicity after aminoglycoside administration and has a prevalence of 1 in 500. Current genetic testing can take over 24 hours, an unacceptable delay in the acute setting. This prospective-observational trial will implement a rapid point of care test (POCT), facilitating tailored antibiotic prescribing to avoid hearing loss.

**Methods and analysis:**

The genedrive POCT can detect the m.1555A>G variant in 26 min from buccal swab. This system will be integrated into the clinical pathways at two large UK neonatal centres over a minimum 6-month period. The primary outcome is the number of neonates successfully tested for the variant out of all babies prescribed antibiotics. As a secondary outcome, clinical timings will be compared with data collected prior to implementation, measuring the impact on routine practice.

**Ethics and dissemination:**

Approval for the trial was granted by the Research Ethics Committee (REC) and Human Research Authority in August 2019. Results will be published in full on completion of the study.

**Trial registration number:**

ISRCTN13704894.

**Protocol version:**

V 1.3.

Strengths and limitations of this studyThis manuscript describes a prospective observational implementation trial of a rapid genetic point of care test (POCT) in the acute neonatal setting to tailor antibiotic therapy, aiming to reduce aminoglycoside-induced hearing loss.We embed a genetic POCT within the admission pathways of two neonatal intensive care units and, due to time pressure, prospective consenting is not possible, requiring the implementation of a unique ethical framework described within the protocol.To our knowledge this is the first example of a genetic POCT implemented in the acute neonatal setting to alter management.Rather than assessing the characteristics or performance of the assay itself during the trial, the primary and secondary outcomes focused on the utilisation of the system and whether normal clinical practice was impacted following implementation.A limitation is that, given the relatively rare nature of the variant (1 in 500), it may transpire that the variant is never detected throughout the study, meaning some secondary outcomes cannot be reliably assessed.

## Background

Aminoglycosides are broad-spectrum antibiotics which act by binding to the 16S rRNA component of the bacterial 30S ribosomal subunit, resulting in the translation of truncated proteins.^1 2^ These abnormal proteins stimulate a stress response within the bacteria culminating in cell death. Due to their low cost and effectiveness, they are one of the most frequently prescribed medicines globally.^3^ The National Institute for Health and Care Excellence (NICE) advises the use of intravenous benzylpenicillin with gentamicin as the first-choice antibiotic regimen for empirical treatment of infection in the neonatal period.^4^ This combination has the major advantage of having a narrow spectrum of activity and lower risk of antibiotic resistance compared with alternative antibiotic regimens, such as third generation cephalosporins which are recommended as second line agents.

The side effect profile from protracted courses of aminoglycosides is well known, with nephrotoxicity and ototoxicity commonly recognised in cohorts who receive large amounts of aminoglycoside.^5^ An ototoxic compound is one that can cause damage to the auditory system (cochleotoxicity) or, less commonly, vestibular system (vestibulotoxicity). Careful analysis revealed that aminoglycoside-induced ototoxicity (AIO) clusters within families and this trait seemed to be transmitted maternally, suggesting mitochondrial inheritance. Further work demonstrated that this susceptibility was caused by a variant in the 12S rRNA (RNR1), m.1555A>G.^6^ This causes a change in the conformation of the 12S rRNA, producing a structure more like the bacterial 16S rRNA, meaning aminoglycosides can more readily bind causing cellular toxicity. The impact of this aberrant binding is most apparent in the inner ear hair cells, leading to ototoxicity.

The m.1555A>G variant is strongly associated with AIO and has a reported prevalence of 0.2% (~1 in 500).^7^ It has previously been suggested that genetic testing should be used in children requiring aminoglycosides to prevent hearing loss and that this approach would be cost-effective when balanced against the costs of lifelong deafness.^3 7^ In many centres, children with cystic fibrosis are tested for the variant at diagnosis as it is expected that these individuals will require aminoglycoside antibiotics at some stage in their lives. This is typically undertaken by a validated genotyping assay in an accredited diagnostic laboratory, a strategy which takes approximately 3–4 days to return a result. Understandably, this testing strategy is not suitable for use in clinical settings where administration of antibiotics is required within an hour of the decision to start treatment with antibiotics.

Currently, there is an inability to test for the m.1555A>G variant in the acute setting such as babies admitted to the neonatal intensive care unit (NICU), representing approximately 90 000 admissions per year in the UK alone. By introducing a simple genetic point of care test (POCT) with a result in under 30 min, we have the potential to avoid approximately 180 cases of severe/profound irreversible deafness every year in the UK alone. Those babies with the m.1555A>G variant could be prescribed an equally effective second line antibiotic, such as a cephalosporin. The UK NICE guidance for early onset neonatal infection recommends a combination of gentamicin and benzylpenicillin as first-line therapy not due to superiority over other agents on an individual patient level, but because that regimen has a narrower spectrum of activity and therefore does not readily contribute towards the development of resistant bacterial pathogens.^4^

Alongside an industry partner, genedrive, we have a developed a small and robust thermocycler platform for rapid point-of-care diagnostic testing of the m.1555A>G variant which has been CE certified for clinical use. This protocol describes a multi-centre prospective observational trial to assess the implementation of the POCT in the clinical setting.

## Methods

### Study design

Investigator-initiated, multi-centre, prospective-observational, implementation trial. Two study sites, both of which are recruiting and experimental.

### Primary objective

To critically assess the performance of a newly developed genetic POCT for use on the NICU and measure whether the clinical teams can integrate the test into their clinical practice without disrupting normal standard of care, facilitating tailored antibiotic prescribing.

### Secondary objectives

Exploratory objectives include an assessment of the wider impact of the implementation, including impact on resources and clinical timelines. We will also assess instances where the assay was not used and consider reasons for deviation. The reliability of the assay itself will also be measured through regular monitoring of results, assessment of test failures and confirmation against gold-standard genotyping.

### Study centres and time schedule

Participants will be recruited from two large UK based NICUs in the UK, Manchester University National Health Service (NHS) Foundation Trust and Liverpool Women’s NHS Foundation Trust (LWH). Both sites will recruit participants and conduct the trial. It should be noted that there is considerable variation in antimicrobial prescribing practices both between and within different countries. The type of antibiotics used, dosing regimens and monitoring protocols can vary between different nations, cities and institutions.^8^ Both units in this study use a combination of a beta-lactam and an aminoglycoside as first line therapy for early onset neonatal infection. Based on historical data, the majority of admissions to both units will be screened for infection and, as such, considered for antibiotic therapy. The trial began in January 2020 and the last participant was recruited in November 2020. The study continued despite the SARS-CoV-2 pandemic.

### Primary outcome

The primary outcome is the number of neonates who are successfully tested for the m.1555A>G variant via this novel POCT genetic test as a proportion of all babies who receive aminoglycoside antibiotics on the two participating NICUs.

### Secondary outcomes

This trial will also assess several secondary outcomes including the total number of neonates identified with the m.1555A>G genetic variant (positive result) as a proportion of the study population. An assessment of resource impact will be undertaken, including a health economic analysis of additional staff time to secure sample and testing and costs associated with alternative antibiotic prescribing for any positive tests. We will record the number of neonates where testing was not undertaken and the rationale for this. Correlation of the POCT result with the current in-house reference assay will be assessed and any test fails will be reported. In the acute neonatal setting, delivering antibiotics in a timely manner is critical and this should ideally be within an hour after admission. As such, we will assess whether the time to antibiotic administration after admission is impacted by implementation of the genetic POCT. A reference time to antibiotic was measured over a month-long period before implementation.

### Inclusion criteria

All babies admitted to NICU across the two participating sites, commencing from the trial start date. This includes babies admitted directly from delivery suite, midwifery led units or transferred from another neonatal unit. At the LWH site, babies who are screened for infection on the NICU but then transferred to external wards (not formally admitted to NICU) will also be included. It is a clinical decision whether the babies are being screened for infection as part of their assessment, reflecting the real-world, pragmatic, nature of the trial. This also reflects the variation in admission procedures between the two trial sites where pathways differ due to local practices.

Given that all babies admitted to NICU are eligible for recruitment, some of those recruited will not go onto receive antibiotic therapy. If the baby did not go onto receive antibiotics, their data will still form part of the dataset for analysis.

### Exclusion criteria

Babies requiring antibiotics immediately, as determined by the admitting clinician, with already established intravenous access. These exclusion criteria recognise the potential urgency of any decision to deliver antibiotics. If intravenous access has not been achieved, then this may provide time to run the assay. We expect that only a small proportion of admissions would be excluded based on these criteria.

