### Testing process and assessment

Participants will be recruited as they are admitted or reviewed by the NICU team. Given the acute nature of the project and the timeframes involved, there is no opportunity to undertake a formal pretrial screening assessment or prospective consenting process. All babies admitted to NICU or screened for infection by the NICU team will be deemed eligible for recruitment unless there is a clinical decision by the responsible admitting clinician that the exclusion criterion is met and the individual requires immediate antibiotic therapy, without delay.

Following recruitment, the time that a decision was made to prescribe antibiotics represents time 0 (figure 1). If antibiotics were not prescribed, then time 0 is represented by the time of admission. The genetic POCT is performed from a buccal swab. When babies are admitted to NICU several swabs are already taken at admission. Where babies are recruited to the study, the m.1555A>G buccal swab will be performed alongside these normal admission processes. The assay will be commenced, and normal practice will continue. Once the assay result is available, it can be used to then undertake personalised antibiotic prescribing, avoiding aminoglycoside antibiotics if the m.1555A>G variant is detected. The CE certified assay will be integrated into the admission pathways at both centres and clinicians will not be blinded to the results.

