**Figure 1 F1:**
[figure not shown]
Flow diagram demonstrating the admission, testing and prescribing process in the Pharmacogenetics to Avoid Loss of Hearing trial. The time that a decision was made to prescribe antibiotics represents time 0. If antibiotics were not prescribed, then time 0 is represented by the time of admission. POCT, point of care test.

As part of the study the following variables will be recorded; participant demographics, admission time, time of decision to prescribe, time swab taken, time assay started, time of assay result, assay result, time of antibiotic prescription, antibiotics prescribed. Where a positive result is identified and antibiotic therapy is required, an alternative antibiotic regimen (standard non-gentamicin pathway as per hospital guidelines) will be prescribed and a referral should be made to clinical genetics for familial cascade testing. Where there is a test-fail, standard of care should be followed, that is, the baby should be administered gentamicin if clinically indicated. Negative results will not be formally reported to the parents. However, all parents will be provided with information on the study in their information pack, allowing them to contact the study team for further information if they wish.

Assay performance will be assessed throughout the study, with at least 10% of samples each month tested via gold-standard sequencing. Any positive samples will also be confirmed as per standard clinical pathways. Any divergence between the POCT and gold-standard methodology will be reviewed by the trial management committee.

Data collection will be undertaken contemporaneously by the clinical staff and any missing data will be collected by the NICU research nurses. Data will be entered into an electronic database by the clinical team and a study ID will be generated. The participants will subsequently be anonymised to the research team. If an individual is not tested for any reason (eg, test overlooked, staff availability or the individual meets the exclusion criteria), these incidences will be captured retrospectively by NICU research nurses by checking daily admission records and the reasons will be documented.

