### Statistical analysis

For the primary outcome, simple descriptive statistics will be used to provide a metric for the proportion of babies tested for the variant over the number who were ultimately prescribed aminoglycoside antibiotics.

Regarding the secondary outcome measures, the objective is to establish that the introduction of the POCT does not significantly impact the time between admission to NICU and the prescription of antibiotics for acute admissions. For the purposes of this analysis, those babies receiving antibiotics within the first 2 hours of admission, representing acute antibiotic administration, will be compared. The burden of proof rests on the research hypothesis, meaning the null hypothesis is that the new POCT does impact this quantity. This is a so-called non-inferiority significance test. The quantity of interest is the mean difference between the admission to ICU and prescription of antibiotics timestamps in two situations: with and without the POCT test 
$\left(\mu_{c},\mu_{t}\right)$
. The null hypothesis is that the difference between these quantities is greater than or equal to some prespecified margin 
(Δ)
 that is, 
$H_{0}:\mu_{c}-\mu_{t}\geq \Delta ;H_{A}:U_{t}-U_{c}<\Delta$
. A type I error here is concluding the time durations are equivalent when in fact the time to antibiotic with the POCT is greater.

The two samples are of unequal size, with the control (‘before implementation’) sample having about 
$n_{c}$
=50, and a forecasted test sample size of around 
$n_{t}$
=900. We also have no insight into population variance and cannot assume they are the same in both groups (it may eg, take some staff members longer to carry out the new test than others). As such, a one-sided Welch t-test will be used to reject or not reject the null hypothesis.

Throughout the study we anticipate that there will be iterative updates to the POCT technology, as avenues for optimisation emerge because of our findings from real-world implementation. The timings of these updates will be recorded and separate post-hoc statistical analysis will be undertaken to assess the impact of each update.

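### The immediate-antibiotics exclusion is written for the POCT period only, so the before-and-after timing samples may be selected differently, with a likely bias against non-inferiority

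*Protocol article*

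**What the plan says.** Inclusion criteria sets eligibility as "All babies admitted to NICU across the two participating sites, commencing from the trial start date". Exclusion criteria then removes "Babies requiring antibiotics immediately, as determined by the admitting clinician, with already established intravenous access", and adds: "We expect that only a small proportion of admissions would be excluded based on these criteria". No number is given. Testing process and assessment places this decision at recruitment: every baby is eligible "unless there is a clinical decision by the responsible admitting clinician that the exclusion criterion is met".

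The control data are described in one sentence of Secondary outcomes: "A reference time to antibiotic was measured over a month-long period before implementation". Statistical analysis puts this sample at about 50 babies and the forecast test sample at about 900. It states one selection rule for the comparison: "those babies receiving antibiotics within the first 2 hours of admission, representing acute antibiotic administration, will be compared".

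The text after Figure 1 deals with babies who are not tested, including where "the individual meets the exclusion criteria". For them, "these incidences will be captured retrospectively by NICU research nurses by checking daily admission records and the reasons will be documented". It does not say that their antibiotic times enter the timing comparison.

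**The concern.** The timing comparison is the article's only specified hypothesis test and the only analysis with a power calculation. Its purpose is to attribute any change in time to antibiotics to the POCT, so the two samples should be selected alike apart from the POCT.

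A baby judged to need antibiotics at once, with access already in place, would normally be treated early in the 2-hour window. The 2-hour filter therefore keeps such babies wherever they have not been removed beforehand. If the exclusion removes them in the POCT period and nothing removes their counterparts in the reference month, the POCT-period mean rises through selection alone. The estimated delay would then mix a POCT effect with case mix, and a test that slows nobody could fail to show non-inferiority.

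**Working it through.** **Inputs from the article (Samples size; Statistical analysis).** One-sided Welch t-test at 5%; margin d = 0.5, about 7 min; 50 controls; 112 test babies stated as needed for 90% power; about 95% power stated at 900. The implied SD is 7 / 0.5 = 14 min.

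**Reproducing the stated figures.**
- Normal formula with 50 controls fixed: 1/n_t = (0.5 / (1.645 + 1.282))² − 1/50, which gives n_t = 109. Welch power needs 115. The stated 112 lies between them.
- At 50 versus 900, SE = 14 × √(1/50 + 1/900) = 2.03 min. Normal power is Φ(7/2.03 − 1.645) = 96.4%, and Welch power is 96.0%. This agrees with the stated figure of around 95%.

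The power calculation itself is sound, and this point does not alter it.

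**Shift caused by one-sided exclusion.** Let f be the share of the POCT-period timing sample removed, and g the minutes by which removed babies are faster than those kept. If the kept babies have mean m, the full set has mean (1 − f)m + f(m − g) = m − fg. Dropping the fast babies therefore raises the mean by f × g. Welch power at no true delay is then computed with 7 − fg in place of 7. Both f and g are assumptions.

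The last column is a plausibility check. A subgroup of share f lying g minutes from the rest contributes f(1 − f)g² to the variance, compared here with 14² = 196.

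| f | g (min) | Shift (min) | % of margin | Power | % of variance used |
|---|---|---|---|---|---|
| – | – | 0 | 0 | 96.0% | – |
| 1% | 10 | 0.1 | 1.4 | 95.6% | 0.5 |
| 1% | 40 | 0.4 | 5.7 | 94.1% | 8 |
| 5% | 10 | 0.5 | 7.1 | 93.5% | 2 |
| 5% | 20 | 1.0 | 14.3 | 89.8% | 10 |
| 5% | 30 | 1.5 | 21.4 | 84.7% | 22 |
| 5% | 40 | 2.0 | 28.6 | 78.3% | 39 |
| 10% | 30 | 3.0 | 42.9 | 61.7% | 41 |
| 10% | 40 | 4.0 | 57.1 | 42.5% | 73 |

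The 10% rows are shown for completeness only. They ask one small subgroup to supply 41–73% of the implied variance. The 5% × 40 min row, at 39%, is already demanding, so it marks the upper end of the range rather than an expected case.

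**Direction.** At a true delay of 7 min, the chance of wrongly declaring non-inferiority is 5.0% with no shift. It falls to 1.7% with a 1-min upward shift and 0.4% with 2 min. It would rise, to 12.3% and 25.0% for the same shifts downward, only if excluded babies were slower than the rest. An exclusion defined by immediate need and existing access makes that unlikely.

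**The case against.** Four arguments stand on the other side.

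1. *The article does not say how the roughly 50 controls were chosen.* A reader might infer that the reference month could not have applied the exclusion. The article does not support that: urgency and intravenous access are clinical states that existed before the POCT, and an approximate rule might be applied from records. What stands is narrower, namely that no equivalent rule is stated.

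2. *The article does not expressly remove excluded babies from the timing set.* The 2-hour filter is worded for both samples and does not require a test result. This is fair, so it cannot be asserted that the samples do differ. But the exclusion bars these babies from recruitment, the forecast 900 is the trial sample, and nothing returns their times to the comparison. Omission is the natural reading. Nor is this only detail left to a fuller document: the exclusion, the control source and the filter are all stated, and together they describe unequal sets.

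3. *The bias is conservative and the outcome secondary.* This stands. A reader might infer a risk of falsely clearing the POCT, or call the estimated delay uninterpretable. Neither follows: the likely direction is known and works against non-inferiority, and the primary outcome does not depend on this test.

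4. *Adding untested babies to the comparison dilutes a real delay, which favours non-inferiority.* This also stands. The untested share is not given, so the dilution cannot be called slight. It is the reason for reporting the comparison both ways.

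**Conclusion.** The point holds as a gap in how the two timing samples are defined. The exclusion is stated for one period, no counterpart is stated for the other, and the shared 2-hour filter does not restore balance. The likely consequence is a POCT-period mean that is somewhat too high, with reduced power and an overstated delay.

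The size depends on two quantities the article does not give. For 1–5% excluded and 10–40 min faster, the shift is 0.1–2.0 min, and power falls from 96% to between 95.6% and 78%. These figures assume a common SD of 14 min, 50 controls, 900 test babies, and excluded babies who are faster than the rest. The expectation of few exclusions refers to all admissions. The share among babies treated within 2 hours may be larger, because every excluded baby needs antibiotics whereas some recruited babies receive none.

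The change is worth making because it is cheap and concerns the only specified hypothesis test. It is not a threat to the trial's main result.

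**What to change.** Define both timing samples by the same rule: all babies given antibiotics within 2 hours of admission in each period, including POCT-period babies who met the exclusion. Retrieve the admission and antibiotic times for those babies, whom research nurses already identify from daily admission records. Report how many there were and their times. State whether any comparable selection was applied in the reference month.

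Report the comparison both with and without excluded and untested babies, and say in advance that the first can dilute a real delay while the second can carry the selection shift described here. Agreement between the two would settle the matter; disagreement should be discussed openly.

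The cost is some wording and a limited retrieval of timestamps. The exclusion itself and clinical practice are untouched. Trial status says recruitment has closed and analysis is ongoing, so the change can still be made to the analysis definition. It should be recorded as made after recruitment ended.
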